## Introduction

Cerebral small vessel disease (CSVD) is a major cause of ischemic stroke and contributes substantially to vascular cognitive impairment and subsequent dementia, accounting for approximately one quarter of ischemic strokes and vascular dementias [1]. Key neuroimaging correlates of CSVD include white matter hyperintensities (WMH), cerebral microbleeds, lacunes, perivascular spaces, and superficial siderosis, which can be assessed by brain magnetic resonance imaging (MRI) [1, 2]. Hence, brain MRI is considered the diagnostic reference standard and also allows quantitative assessment of CSVD burden, including volumetric evaluations [2, 3]. Advanced MRI techniques such as diffusion tensor imaging (DTI), amongst other techniques, can enable further characterization of microstructural white matter injury beyond conventional WMH assessment [4, 5].

Recent neuroimaging studies indicated that CSVD may show mild partial regression in an observation over several years, highlighting the dynamic nature of the disease [6, 7]. From a therapeutic perspective, evidence supports antihypertensive treatment as a secondary preventive strategy [1, 4]. In addition, randomized clinical trials suggest that pharmacological approaches such as the combination of cilostazol and isosorbide mononitrate may reduce stroke recurrence and improve functional and cognitive outcomes, although the generalizability of these findings is uncertain [8]. Longitudinal observational studies suggest that WMH progression may be accelerated following lacunar stroke compared with asymptomatic individuals, particularly in patients with higher baseline CSVD burden [9, 10]. With higher degrees of dysconnectivity as a result of acute stroke and preexisting CSVD affecting deep WM, functional outcome is worse [11]. However, available data are based on datasets of observational and interventional prospective trials on CSVD or ischemic stroke and do not adequately clarify how stroke mechanism, size, and localization impact on CSVD progression [12, 13].

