#### Sample size

We aim to include 60 patients in the three study groups, resulting in a maximum total number of 180 patients. We expect a drop-out proportion of 25%, relating to difficulties of mobility and morbidity for adherence in follow-up visits of patients with territorial brain ischemia in particular and considering the rural area surrounding the region of Ulm, Baden-Württemberg, Germany. The calculation of sample size is not based on a confirmatory study aim, but is exploratory and mirrors our experiences made in the pilot study of the recruitment that can be expected and delivered in our clinical setting in Ulm.

As an illustration of sensitivity: in a pilot subset (unpublished data) with paired manual WMH volumetry (17 patients), the mean 12-month WMH volume change was 5.30 mL (SD 6.03; standardized within-subject effect d_z ≈ 0.88). A within-group comparison detects a change of this magnitude at ~ 80% power (two-sided α = 0.05) in ~ 10 patients per group. With 60 patients per group (≈ 45 completing follow-up after the anticipated 25% drop-out), the planned cohort is sensitive to within-subject WMH changes as small as d_z ≈ 0.36 (at 60 per group) to 0.42 (at 45 per group), i.e. ≈ 2.2–2.5 mL, well below the 5.30 mL observed in the pilot data, and, for exploratory between-group comparisons, to standardized differences of d ≈ 0.51 (at 60 per group) to 0.59 (at 45 per group), a ≈ 3.1–3.6 mL difference in WMH change between groups.

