### Statistical methods

#### Methods of analyses

The statistical analysis will be purely descriptive. Categorical variables will be summarized using absolute and relative frequencies, while continuous variables will be described using the mean and standard deviation or the median, interquartile range, and minimum and maximum values, as appropriate. Group differences will be assessed according to the measurement scale and distribution using the t-test or Wilcoxon signed rank test for continuous variables, and the chi-square test or Fisher’s exact test for categorical variables. To investigate temporal changes in parameters, individual slopes will first be estimated using linear mixed-effects models with random intercepts for participants to account for within-subject correlation. They will be subsequently compared between groups. In a further step, notable group differences will be explored using appropriate regression methods (linear regression, logistic regression, and, if applicable, mixed-effects models).

Differences in follow-up imaging with regard to the number and volume of radiological markers of CSVD will be analyzed using the Wilcoxon rank-sum test. Associations between continuous variables will be examined using scatter plots; where appropriate, Pearson or Spearman correlation coefficients will be calculated. Longitudinal data (e.g. the course of one or more biomarkers) will be illustrated by scatter/dotted plots and spaghetti plots, as appropriate. All statistical tests will be conducted using a two-sided significance level of α = 0.05. No adjustment for multiple testing will be performed. Given the exploratory nature of the study, all statistical test results will be interpreted as hypothesis-generating rather than confirmatory. Statistical analyses will be performed with R, The R Project for Statistical Computing with the latest version available (currently 4.5.3).

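### Non-randomised groups are compared without adjustment, and regression follows only if a crude difference is 'notable', so imbalance could create or mask differences in WMH change and biomarker course

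*Protocol article*

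**What the plan says.** The Methods of analyses section of the protocol article sets an order of work.

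- **Group differences** are first assessed with a t-test or a Wilcoxon test, or with a chi-square or Fisher test. The number and volume of imaging markers go to the Wilcoxon rank-sum test. The primary outcome, change in WMH volume, is an imaging volume.
- **Slopes** come from random-intercept mixed models, for which no covariate is named, and are then compared between groups.
- **Regression** follows on a condition: "In a further step, notable group differences will be explored using appropriate regression methods". The section does not define the condition, and it lists no covariates for this step either.
- **Associations between continuous variables** are examined by scatter plot, and "where appropriate, Pearson or Spearman correlation coefficients will be calculated". No stratification or adjustment by group is mentioned.
- **Testing:** "All statistical tests will be conducted using a two-sided significance level of α = 0.05". Results are labelled hypothesis-generating.

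Under Eligibility criteria, the groups are defined by stroke pattern on MRI, and each admits Fazekas grades 1 to 3 and any adult age. Under Recruitment, Group 1 comes from a specialised outpatient clinic, while Groups 2 and 3 are recruited as inpatients.

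**The concern.** Groups formed by diagnosis and drawn from different settings may differ in age, vascular risk factors and WMH burden at entry. If such a factor also predicts WMH change, a crude contrast mixes the effect of stroke type with who enters each group. The condition on regression adds a second problem. An imbalance that works against a real difference makes the crude contrast small, and a small contrast is the one least likely to be called notable and taken further.

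The biomarker question is exposed in its own way. The first stated objective is to find one or more blood markers that help identify CSVD progression. The Introduction reports that, after a recent small subcortical infarct, NfL was raised shortly after the stroke and until 3 months, and was back to normal at 15 months. Samples are taken at 0, 3, 6 and 12 months, so early samples in Groups 2 and 3 can carry an infarct signal that Group 1 lacks. A correlation that ignores group could reflect that signal rather than CSVD activity.

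**Working it through.** **Inputs from the Sample size section.** The pilot gives "the mean 12-month WMH volume change was 5.30 mL (SD 6.03; standardized within-subject effect d_z ≈ 0.88", from 17 patients. The planned size is 60 per group, or 45 after 25% drop-out. The stated between-group sensitivity is "to standardized differences of d ≈ 0.51 (at 60 per group) to 0.59 (at 45 per group"), or 3.1–3.6 mL.

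**Step 1: reproduce the plan's figures.**
- d_z = 5.30 / 6.03 = 0.88.
- Detectable d at 80% power = (1.960 + 0.842) × √(2/n). This is 0.511 for n = 60 and 0.591 for n = 45.
- Times 6.03, these are 3.1 and 3.6 mL. The stated figures are right, and they refer to an unadjusted comparison.

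**Step 2: possible bias.** The documents give no correlation between a baseline factor and WMH change, and no group imbalance, so both are assumed. If a factor has within-group correlation r with change, and two groups differ on it by D standard deviations, the crude difference is shifted by r × D × 6.03 mL:

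| r | D = 0.3 | D = 0.5 |
|---|---|---|
| 0.3 | 0.54 mL | 0.90 mL |
| 0.5 | 0.90 mL | 1.51 mL |
| 0.6 | 1.09 mL | 1.81 mL |

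The range is about 0.5–1.8 mL.

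**Step 3: effect on the tests.** This uses 45 per group, D = 0.5 and two-sided α = 0.05. Crude figures are from the t-test (noncentral t, except that the 54% and 36% lie within about two points of both the noncentral-t and simulated values). Adjusted figures and the last row come from 4,000 simulated studies in which the factor is a true confounder and the linear model is correct.

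| | r = 0.3 | r = 0.5 |
|---|---|---|
| No true difference: crude test rejects | 10.8% | 21.6% |
| No true difference: adjusted test rejects | about 5% | about 5% |
| True d = 0.59, opposing imbalance: crude power (about 80% if balanced) | about 54% | about 36% |
| Same: adjusted power | about 79% | about 87% |
| Same: significant only after adjustment | 26% | 52% |

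The last row is the share of studies that the condition would hold back if notable were taken to mean significant.

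**Step 4: precision.** With the t-distribution, the unadjusted detectable difference at 45 per group is 0.597 × 6.03 = 3.60 mL. Adjustment multiplies it by √(1 − r²), but imbalance multiplies it by about √(1 + D²/4), which is 1.03 at D = 0.5.
- r = 0.3: 3.60 × 0.954 × 1.031 = 3.54 mL.
- r = 0.6: 3.60 × 0.800 × 1.031 = 2.97 mL.

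At the lower correlation the gain is almost nil.

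**The case against.** **The article is condensed, and an unseen analysis plan may list covariates.** This is fair as to the list, and such a plan could also add adjustment. A reader might infer that masked differences will never be adjusted; that goes too far. What the article does fix is that regression depends on the crude result, and that is a choice already made.

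**The study is exploratory, and its second aim is to describe differences in biomarker courses.** Unadjusted contrasts are legitimate as description. The label lowers the claim made for a p-value but does not remove bias, and a confounded signal suggests the wrong hypothesis.

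**The Introduction does not establish baseline burden as a confounder.** It says that "WMH progression may be accelerated following lacunar stroke compared with asymptomatic individuals, particularly in patients with higher baseline CSVD burden". That describes how burden modifies the effect of stroke more than a main effect of burden, and a main-effects model would not address it. This stands. The confounding risk rests on how the groups are formed.

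**The text says neither that correlations are pooled nor that significance is the filter.** Both are inferences. The text names no stratification and leaves the filter undefined. On the imaging side, the Postprocessing section already excludes acute DWI lesions from WMH volume at all three MRI visits, so the infarct problem concerns the blood markers.

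**Adjustment has its own difficulties.** Adjusting change for baseline in non-randomised groups can mislead (Lord's paradox). Blood pressure in Groups 2 and 3 is measured after the stroke and may be a consequence of it. DWI lesion volume is zero in Group 1 by definition. All three points stand and shape the fix.

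**Conclusion.** The point holds as a design weakness in the stated analysis sequence. Followed as written, the plan can report differences that reflect group composition, can leave masked differences unexamined, and offers only simple correlations for its first objective. Confounding is a justified risk here, not a demonstrated fact, because the documents report no imbalance and no correlation. Under the assumed ranges the bias is about 0.5–1.8 mL; the upper end is half of the 3.6 mL detectable at 45 per group (1.8 / 3.6 = 0.50). It also relies on an SD from 17 pilot patients. A reader might also infer that adjustment sharpens the comparison for free. Step 4 does not support that, since at r = 0.3 and D = 0.5 the detectable difference moves only from 3.60 to 3.54 mL. The sample-size figures themselves are not in question.

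**What to change.** 1. **Remove the condition.** Compare 12-month WMH change between groups in a linear model fitted whatever the crude result, with covariates already collected: at least age, sex and history of vascular risk factors. Show the unadjusted estimate alongside.
2. **Add a model with baseline WMH volume as a stated additional analysis**, with a sentence justifying adjustment of change for baseline in non-randomised groups.
3. **For the biomarker objective**, regress WMH change on the log biomarker with group and age, adding baseline DWI lesion volume within Groups 2 and 3. Alternatively, report correlations within each group. Do not rely on a single unadjusted correlation.

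The cost is wording, some extra analysis and a few degrees of freedom. With 3 × 45 = 135 completers, an intercept, two group terms, age, sex and four yes/no risk factors use 9, leaving 126. Nine patients had been enrolled by 11 June 2026, after a March 2026 start, so none could yet have 12-month data and the change can still be prespecified. Results remain exploratory.

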### Primary outcome

The primary outcome is the change in WMH volume based on brain MRI measurements.

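### The rank-sum test named for WMH volume uses only patients scanned at the visit analysed, although 25% drop-out is expected, in particular after territorial stroke

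*Protocol article*

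**What the plan says.** All places are in the protocol article.

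- Primary outcome: "The primary outcome is the change in WMH volume based on brain MRI measurements". The Sample size section illustrates it with the 12-month change in a pilot subset. Table 2 and the Postprocessing section place MRI at baseline, month 6 and month 12.
- Methods of analyses, on imaging: "Differences in follow-up imaging with regard to the number and volume of radiological markers of CSVD will be analyzed using the Wilcoxon rank-sum test". No visit is named.
- The same section plans linear mixed-effects models with random intercepts for temporal changes in parameters generally. Individual slopes are to be taken from them and compared between groups. The text does not say whether this model or the rank-sum test leads for WMH volume.
- Sample size: 25% drop-out is expected, "relating to difficulties of mobility and morbidity for adherence in follow-up visits of patients with territorial brain ischemia in particular". The rural catchment is given as a further reason. No rates per group are stated, and about 45 completers are assumed in every group.
- The study is described as exploratory and its tests as hypothesis-generating.

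**The concern.** A rank-sum test compares two sets of observed values. A patient without the scan at that visit drops out of it, and in a month-12 comparison that patient's month-6 scan adds nothing. This is harmless only if those lost progress like those who stay. The plan itself expects loss that is related to illness and falls on one study group in particular, so that condition cannot be taken for granted.

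At stake are the size of WMH change within Group 3 and every comparison of Group 3 with Groups 1 and 2. Describing an outcome as exploratory does not protect its estimate from selection.

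The mixed model could use the month-6 scans, but as written it has its own gap. With random intercepts only, patients differ in level and share one slope, so the model contains no individual slopes to compare.

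**Working it through.** **Inputs from the article.** Pilot 12-month change 5.30 mL, SD 6.03; 60 enrolled per group; 25% drop-out; 80% power; two-sided alpha 0.05; MRI at months 0, 6 and 12.

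**Inputs not in the article, so assumed.** Drop-out p in each group, and δ, the mean WMH change in lost patients minus that in scanned patients.

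**Step 1: the plan's own figures** (normal approximation, 1.960 + 0.842 = 2.802).

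- d_z = 5.30/6.03 = 0.879; n = (2.802/0.879)² = 10.2.
- Completers: 60 × 0.75 = 45.
- Within group: 2.802/√60 = 0.362 (2.18 mL); 2.802/√45 = 0.418 (2.52 mL).
- Between groups: 2.802 × √(2/60) = 0.511 (3.08 mL); 2.802 × √(2/45) = 0.591 (3.56 mL).

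These agree with the article. They treat drop-out only as a loss of numbers, equal in each group.

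**Step 2: error from using scanned patients only.** The true mean is (1 − p) × (mean in scanned) + p × (mean in lost), so the scanned-only mean is off by −p × δ. With the same δ in all groups, the difference between Group 3 and another group is off by −(p3 − p_other) × δ. Each drop-out split below averages 25% over three equal groups.

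| Drop-out, Group 3 / others | δ (mL) | Error, Group 3 mean (mL) | Error, group difference (mL) |
|---|---|---|---|
| 25% / 25% | −3 | +0.75 | 0 |
| 25% / 25% | +6.03 | −1.51 | 0 |
| 35% / 20% | −3 | +1.05 | +0.45 |
| 35% / 20% | +6.03 | −2.11 | −0.90 |
| 45% / 15% | −3 | +1.35 | +0.90 |
| 45% / 15% | +6.03 | −2.71 | −1.81 |

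With δ = 0 every error is zero. Equal drop-out protects the comparison only if δ is also equal: at 25% everywhere, δ = 3 mL in Group 3 and 0 elsewhere gives −0.25 × 3 = −0.75 mL.

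These are errors in means. A rank test responds to the same selection, but its statistic is not in mL.

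**Step 3: does the planned mixed model repair it?** A simulation used 60 patients in one group and 60 runs per setting. Assumed values were a true 12-month change averaging 5.30 mL (SD 5), half of it reached by month 6, and measurement error SD 1.5 mL per scan. All drop-outs had a month-6 scan. The observed 12-month change then has SD √(25 + 2 × 2.25) = 5.43 mL, a little below the pilot's 6.03. Simulation error is about 5.43/√45/√60 = 0.10 mL.

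| Who leaves after month 6 | Drop-out | Completers (mL) | Random intercepts (mL) | Random slopes added (mL) |
|---|---|---|---|---|
| Unrelated to progression | 25% | 5.36 | 5.35 | 5.34 |
| Unrelated to progression | 40% | 5.31 | 5.30 | 5.29 |
| Faster progressors | 25% | 3.91 | 4.49 | 5.31 |
| Faster progressors | 40% | 3.34 | 4.28 | 5.42 |
| Slower progressors | 25% | 6.79 | 6.25 | 5.43 |
| Slower progressors | 40% | 7.48 | 6.52 | 5.32 |

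Where loss depended on the month-6 change, the random-intercept model removed these shares of the completer bias:

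- Faster progressors leave: (4.49 − 3.91)/(5.30 − 3.91) = 42%, and (4.28 − 3.34)/(5.30 − 3.34) = 48%.
- Slower progressors leave: (6.79 − 6.25)/(6.79 − 5.30) = 36%, and (7.48 − 6.52)/(7.48 − 5.30) = 44%.

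Random slopes removed nearly all of it in both directions.

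**The case against.** **The direction is not established.** A reader might infer that WMH change is understated, most of all in Group 3, because the sickest patients leave and also progress fastest. The article does not support this. Its reasons for drop-out are mobility, morbidity and distance, not WMH progression. The Introduction's statement is that "WMH progression may be accelerated following lacunar stroke compared with asymptomatic individuals, particularly in patients with higher baseline CSVD burden", which says nothing about territorial stroke. The same section adds that existing data leave the role of stroke mechanism, size and location unclear. Understatement is plausible, but no bias or the opposite bias is also possible. This objection stands.

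**Drop-out is not said to be mainly territorial, and month 12 is not fixed for the test.** Both are correct. The article gives no group rates, and the rank-sum sentence names no visit. The month-6 scans are unused only if the comparison is made at month 12, the time point of the Sample size illustration.

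**A longitudinal model is already planned, and nothing excludes WMH from it.** This stands in part. The model could use the month-6 scans, but a different test is named for imaging volumes, and random intercepts alone correct only partly (Step 3).

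**The size may be small.** With 40% drop-out in Group 3, 17.5% elsewhere, and loss driven by a baseline severity that correlates 0.2 to 0.5 with WMH change, the spurious difference was −0.2 to −0.5 mL. The estimate's standard deviation was 1.30 to 1.39 mL. All of these inputs are assumed, and only positive correlations were tried.

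**Missing-data handling belongs in the analysis plan.** That is fair for detail, and its absence here is not the point. The point is that the test named in the article fits poorly with the drop-out the article predicts.

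**Conclusion.** The concern holds as a risk of selection bias of unknown direction and size in WMH change and in the comparisons of Group 3 with the other groups.

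At the widest assumptions tried, the spurious group difference reaches 1.81 mL, about half of the 3.56 mL that the plan gives as detectable with 45 per group (1.81/3.56 = 0.51). It is zero if lost and scanned patients progress alike. These figures rest on assumed group drop-out rates and on an assumed δ, neither of which the article supplies. The claim that Group 3 is understated goes beyond the documents.

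The case for change does not depend on the direction. When loss depends on the observed month-6 change, scanned-only and random-intercept analyses err either way, and a model with adequate covariance structure largely corrects both. The tests are hypothesis-generating, so this is a worthwhile improvement and does not threaten the study.

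**What to change.** In Methods of analyses, name one main analysis of WMH change: a repeated-measures mixed model on all available MRI (baseline, months 6 and 12). It should have visit as a category, group-by-visit terms and unstructured covariance (or random slopes), account for baseline WMH volume and age, and report the month-12 contrast between groups. Baseline volume enters either as the first response or as a covariate, not both. If the segmentation pipeline delivers paired change instead of a volume per visit, model the two changes with baseline volume as covariate.

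Keep the rank-sum test in scanned patients as supportive, and name its visit. Add a sensitivity analysis that shifts unobserved changes in both directions, for example by ±3 mL (about half the pilot SD).

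Use NIHSS and mRS only as auxiliary variables for the missing data or in a sensitivity analysis. They partly reflect stroke group, and adjusting for them could distort the group contrast.

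Cost: rewording and slightly more analysis work. The scans are already scheduled, and only nine patients were enrolled by 11 June 2026. The estimate will rely on data being missing at random given the observed scans and covariates, which the shift analysis probes. It cannot recover scans of patients who withdraw and have their data deleted, an option the article gives them.

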Beyond brain MRI, no clinically established in vivo surrogate marker for CSVD activity currently exists. Blood-based biomarkers represent a promising approach for monitoring longitudinal disease activity and potential regression. Of those, serum neurofilament light chain (NfL) levels seem in particular promising as they have been found to reflect imaging burden and neuropsychological features (processing speed performance) of CSVD in a cross-sectional study including more than 500 patients [14]. Furthermore, temporal changes of serum NfL have been described in a monocenter cohort of 79 patients after a recent small subcortical infarct upon 15 months. Compared to healthy controls, NfL levels were increased shortly after stroke and until 3 months, returning to normal levels after 15 months [15]. New incident ischemic lesions on MRI were reflected by secondary NfL increases [15]. Further results from the Alzheimer’s Disease Neuroimaging Initiative (ADNI) showed that plasma NfL correlated positively with CSVD severity, and with the presence of cerebral microbleeds (CMBs) and lacunes [16]. With higher the changes in plasma-NfL were over time, the CSVD burden and WMH increased upon a mean follow-up of 27 months in 378 patients [16]. These findings imply an additional value of blood NfL measurements for disease monitoring, which may be complementary to brain MRI.

In a monocenter, prospective registry, serum GFAP correlated with verbal fluency, visuomotor and executive functions in patients with CSVD [17]. Lately, in a follow-up study over 12 months, vascular endothelial growth factor (VEGF) levels in the blood were associated with incident brain lesions in a longitudinal study [18]. Beyond that, such biomarkers have demonstrated substantial diagnostic and longitudinal value in other neurological disorders, including multiple sclerosis and neurodegenerative diseases [19, 20].

The present prospective cohort study builds upon a previously conducted single-center pilot study by our group (local Ethics approval no. 343/22), which demonstrated the feasibility of longitudinal biomarker measurements in patients with CSVD and provided preliminary evidence supporting associations between biomarker dynamics and MRI-detected CSVD progression.

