The objectives of the presented study include the identification of one blood biomarker or a set of biomarkers that can help identify disease progression in CSVD. A further aim is to describe differences of biomarker courses in direct comparison of patients with CSVD and acute lacunar ischemia with patients with territorial ischemia in a prospective, consecutive and multi-modal trial.

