### Recruitment

The recruitment is carried out by a designated study team of the Department of Neurology, University Hospital Ulm, Germany, during the in-patient stay of patients eligible for participation in Groups 2 and 3. Patients with CSVD without a current stroke are recruited at our specialized outpatient clinic for CSVD and cerebrovascular diseases. As of June 11th, 2026 6 male patients and 3 female patient were enrolled. Of those, 5 (56%) presented with acute territorial stroke and were recruited in Group 3, 3 had a lacunar stroke and were assigned to group 2 (33%) and one further participant without acute stroke was recruited into group 1 (11%). The median age was 68 years with a minimum of 52 and a maximum of 85 years.

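### In the stroke groups the planned straight-line slope starts in the acute phase, and the stated biomarker-to-WMH correlation is unadjusted, so infarct recovery is not separated from CSVD progression

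*Protocol article*

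**What the plan says.** The Introduction sets two biomarker aims. The first is "identification of one blood biomarker or a set of biomarkers that can help identify disease progression in CSVD". The second is to "describe differences of biomarker courses in direct comparison of patients with CSVD and acute lacunar ischemia with patients with territorial ischemia".

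Stroke patients are recruited "during the in-patient stay of patients eligible for participation in Groups 2 and 3"; Group 1 comes from an outpatient clinic (Recruitment). Blood is taken at 0, 3, 6 and 12 months (Biosamples; Table 2). On what to expect after a small subcortical infarct, the Introduction reports: "Compared to healthy controls, NfL levels were increased shortly after stroke and until 3 months, returning to normal levels after 15 months".

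Methods of analyses then gives three steps that bear on biomarkers:

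- Time course: "individual slopes will first be estimated using linear mixed-effects models with random intercepts for participants to account for within-subject correlation". On their use: "They will be subsequently compared between groups".
- Regression, directed at differences between groups: "notable group differences will be explored using appropriate regression methods (linear regression, logistic regression, and, if applicable, mixed-effects models".
- Association: "Associations between continuous variables will be examined using scatter plots; where appropriate, Pearson or Spearman correlation coefficients will be calculated".

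The section names no covariate and does not say whether correlations are pooled over groups or run within them. DWI lesion volume is measured (Postprocessing) but has no stated role in any model.

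**The concern.** In Groups 2 and 3 the month-0 sample lies in the acute stroke phase. By the article's own account NfL is still raised at 3 months and falls later. A slope fitted through 0, 3, 6 and 12 months in these patients therefore contains the decay of the acute rise as well as any CSVD activity. In Group 1 it does not.

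The same difficulty can reach the first objective. A biomarker that mainly reflects the recent infarct differs by group and by infarct size. If WMH change also differs along those lines, an unadjusted correlation run across groups can show a link that exists in no single group. It would be a modest negative one, with steeper biomarker decline accompanying more WMH growth. At stake is which candidate marker the study carries forward.

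**Working it through.** **1. Scale taken from the plan.** The documents give no figure for the biomarker association, so I take the scale for WMH differences from Sample size. Inputs: SD of 12-month WMH change 6.03 mL, 60 enrolled and 45 completing per group, 80% power, two-sided 0.05, so z-sum = 1.960 + 0.842 = 2.802.

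- d = 2.802 × √(2/60) = 0.511; × 6.03 = 3.1 mL
- d = 2.802 × √(2/45) = 0.591; × 6.03 = 3.6 mL

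Both agree with the article. A between-group difference of about 3.0-3.6 mL is thus the size that the plan itself uses to illustrate sensitivity.

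**2. What the slope measures.** For visits at t = 0, 3, 6, 12 the mean is 5.25 and Σ(t − 5.25)² = 27.5625 + 5.0625 + 0.5625 + 45.5625 = 78.75. The least-squares weights (t − 5.25)/78.75 are -0.0667, -0.0286, +0.0095 and +0.0857 per month. The acute baseline carries the second-largest weight.

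Take a peak post-stroke rise of 1 unit and no CSVD change at all. The decay shapes are assumptions, since the documents give no magnitudes:

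| Rise remaining at 0/3/6/12 months | Slope per 12 months | Left at 12 months |
|---|---|---|
| 1 / 1 / 0.5 / 0 | -1.09 | 0 |
| 1 / 1 / 0 / 0 | -1.14 | 0 |
| 1 / 0.8 / 0.6 / 0.2 (straight decline to month 15) | -0.80 | 0.2 |
| 0.6 / 1 / 0.5 / 0.1 | -0.66 | 0.1 |

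First row: 12 × (-0.0667 − 0.0286 + 0.5 × 0.0095) = -1.09. The third row shows that even a straight decay, which a line would fit well, gives a slope made up wholly of recovery.

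Separately, a model with random intercepts only has a common time slope. It does not by itself yield the individual slopes that the text mentions.

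**3. The correlation, if run across groups.** Simulation, 1,500 runs per setting, all on assumptions:

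- The true biomarker-to-CSVD link is zero, and the within-group SD of WMH change is 6.03 mL.
- The acute rise in Groups 1/2/3 averages 0/0.5/1.0 or 0/0.3/1.5 units, varies between patients (log-SD 0.6), and follows the first decay shape above.
- Biomarker noise has SD 0.2, and a true slope with SD 0.1 is unrelated to WMH change.
- Each patient's fitted slope is correlated with WMH change at two-sided 0.05.

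| Mean WMH change, Groups 1/2/3 (mL) | Across groups, n = 45 each | Adjusted for group |
|---|---|---|
| 5.3 / 5.3 / 5.3 | 5-6% | 5-6% |
| 3.8 / 5.3 / 6.8 (range 3.0) | 32-36% | 5-6% |
| 3.5 / 5.3 / 7.1 (range 3.6) | 42-48% | 5-6% |
| 2.2 / 5.3 / 5.3 (range 3.1) | 25-34% | 5-6% |
| 4.3 / 7.3 / 4.3 (lacunar only) | 4-9% | 5% |

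Ranges run over the two patterns of acute rise. In the three ordered settings the mean correlation is -0.11 to -0.16. At 60 per group these settings give 32-61% across groups and 4-6% adjusted; the lacunar-only setting gives 5-10% across groups.

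**4. Is adjustment for group enough?** With equal group means, but infarct size correlated 0.3 with WMH change (assumed), rejection at 45 per group is about 35% across groups and 54% after adjustment for group. Group alone then does not suffice; infarct volume has to enter. A model including it was not simulated.

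**The case against.** Several counter-arguments stand, and they limit the point.

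- A reader might infer that correlations are pooled over the three groups. The text is silent on this, and strata for an exploratory association may well be set out in a full protocol or SAP that is not shown.
- A reader might infer that the slopes are what will be correlated with WMH change. The article states them only for comparing groups. For the lacunar-versus-territorial aim the acute course is of interest in its own right.
- A reader might conclude that the analysis will detect infarct recovery instead of progression. That does not follow. A false association needs WMH change to vary by group or infarct size too. The Introduction says only that progression may be faster after lacunar stroke, and a lacunar-only excess causes little inflation. The acute lesion is also masked out of WMH volume, and Group 1 is unaffected.
- Much higher error rates can be produced by assuming a gap of 1 SD in WMH change. That is 6.03 mL, more than the whole pilot mean change of 5.30 mL, and nothing in the documents supports it.
- Results are declared hypothesis-generating, and spaghetti plots would show an early fall.

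What remains is what the text does state. Masking protects the WMH measure but not the biomarker, and a plot does not remove recovery from a slope. An exploratory label does not help a reader tell which process produced the hypothesis. A reader might also extend the point to change in MoCA; the documents give no course of cognitive recovery on which to base that, so it is left out.

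**Conclusion.** The point holds in a limited form. The stated time model fits poorly with the NfL course that the article itself reports, and in Groups 2 and 3 its slope mixes recovery with CSVD activity, by about -0.7 to -1.1 units per 12 months for each unit of acute rise. The stated association method has no adjustment. If it is applied across groups, the false-positive rate depends on how WMH change differs between them: none beyond the nominal 5% with equal change, 4-10% with a lacunar-only excess, and 25-48% at 45 per group with ordered differences of 3.0-3.6 mL. Decay shapes, biomarker spread and group-specific WMH change are all assumed. The WMH primary outcome itself is not affected. The change should be made, because it costs little and bears on the first-named objective.

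**What to change.** In Methods of analyses:

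1. Model biomarkers with visit as a category (0, 3, 6, 12 months) and a group-by-visit interaction, in place of one linear slope. The acute course stays visible for the lacunar-versus-territorial aim.
2. For the progression objective, regress WMH change on a post-acute biomarker measure, adjusted for group, baseline DWI lesion volume, age and baseline WMH volume. The 12-month level is one choice: under the four shapes above, 0 to 0.2 of the acute rise is left by then, against 0.5 or more at 6 months in three of the four.
3. Show Group 1 separately, since it is free of the acute signal.

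The cost is a few more parameters per model; every variable and visit is already planned. The Group 1 display will be imprecise. From tanh(2.802/√(n − 3)), the correlation detectable at 80% power is 0.41 with 45 patients, against 0.24 with all 135 completers. It should be read as a check on direction and size, with an interval.
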